### Secondary Outcome measures

Secondary outcome measures are clinical response (i.e. 50% reduction in depressive symptoms) on the 29-items SIGH-SAD, the Atypical-8 subset from the SIGH-SAD, the HAMD-6 depression core features subscore, and the MADRS. Specially trained clinical research staff conducted the interviews.

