### Inclusion and exclusion criteria

The inclusion criteria are 60 years or more of age, a primary diagnosis of Major Depressive Disorder according to DSM-IV criteria, as assessed with the Structured Clinical Interview [40] by a trained research physician (RL) or a specially trained research psychologist.

Candidates are not admitted to the study if any of the following criteria were present: (1) insufficient fluency in Dutch, (2) living outside the Amsterdam region, insufficient address for follow-up, or unwillingness to return for follow-up, (3) light treatment in the past, (4) history of light-indicated migraine or epilepsy, (5) presence of physical illnesses that require urgent specialized treatment (e.g. untreated diabetes, malignancies, chronic infections, thyroid problems, eye diseases (glaucoma, cataract) for which surgery is scheduled in near future), (6) the presence of other major axis-I disorders like bipolar disorder, dementia, delirium, all psychotic disorders, PTSD, a recent history of a suicide attempt, the presence of the DSM-IV Seasonal Pattern specifier, (7) diseases that could interfere with HPA-axis functioning, or (8) diseases or medication that could elevate the risk of light-therapy associated side effects (e.g. progressive eye diseases, senile macula degeneration, Lupus, tricyclic antidepressants, tetracyclic antibiotics), (9) current drug or alcohol abuse less than 3 months before the study, (10) any drugs (e.g. corticosteroids, cyclosporin A) known to interfere with endocrine function. Also excluded were all subjects who were taking (11) SSRIs or SNRIs shorter than 2 months.

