### Sample size

Martiny et al. [21] found a moderate effect size (ES>0,50 maximum 0,66) for bright light treated group in comparison with dim light treated group on both self-assessment and observer rating scales in patients with a high prevalence of melancholic depression. Based on the literature on the expected response rate, and using conventional values for α (0.05) and β (0.80), and two-tailed tests with equal groups, the sample size aimed for in the current study is 63 patients per arm [42].

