### Statistical analysis

Data will be analyzed using SPSS 16.0. Analyses are performed using intention-to-treat principles. Therefore, drop-outs are distinguished into 'drop-outs before T1 assessment' and 'drop-outs after T1 assessment'. When only a randomisation assessment (T0) is available, subjects are considered lost to follow-up. For 'drop-outs after T1 assessment' the principle of LOCF (last observation carried forward) will be used. For sensitivity analysis, the more conservative LOCF variant will be calculated where T0-data will be carried forward, and a completers analysis will be performed.

Baseline characteristics across the treatment groups are compared using analysis of variance (ANOVA) and χ^2^-statistics.

As the primary analysis efficacy of treatment is tested by performing a repeated measures analysis of variance (RMANOVA) on HADRS-17 scores at T0, T1 and T2. To control for possible difference in baseline severity scores baseline values for HADRS-17 are used as covariates. Repeated contrasts are applied to compare effects in the treatment period with effects after the treatment period. As secondary analyses efficacy of treatment is tested by performing RMANOVA on the other depression symptom scales (SIGH-SAD scores, HAM-D6, MADRS-scores). As tertiary analyses depression outcome measures are dichotomised to responders and non-responders, where response is defined as a decrease of ≥ 50% on the HADRS-17, HAM-D6, SIGH-SAD and MADRS scales. Responder rates will also be presented as odd's ratios and NNT's.

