### Primary Outcome measure

Depression severity is assessed by a trained research physician and qualified research psychologists (MN, [name]) using the Montgomery-Åsberg Depression Rating Scale (MADRS) [44], the combined 21-item Hamilton and 8-item atypical symptom scales of the Structured Interview Guide for the Hamilton Depression Rating Scale – Seasonal Affective Disorder Version (SIGH-SAD) [45], which although originally designed for SAD studies is equally applicable for assessment of nonseasonal depression with atypical features (as in the present study). The Hamilton and atypical symptom subscales of the SIGH-SAD can be analyzed separately or in combination [46]. The primary outcome measure is depression ratings using the HADRS-17 scale. Response is defined as a 50% reduction in depressive symptoms, on the HADRS-17 scale at T1 and T2. Specially trained clinical research staff conducts the interview.

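### The 50% response rule on the Atypical-8 cannot be computed at a baseline of 0, is met by a one-point fall at 1 or 2, and does not match the analysis section (minor; secondary outcome only)

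*Protocol article*

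**What the plan says.** The Secondary Outcome measures section defines the secondary outcomes as "clinical response (i.e. 50% reduction in depressive symptoms) on the 29-items SIGH-SAD, the Atypical-8 subset from the SIGH-SAD", followed by the HAMD-6 and the MADRS. It gives no minimum baseline score and no rule for a baseline of 0.

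The Inclusion and exclusion criteria section sets entry by age and diagnosis: "The inclusion criteria are 60 years or more of age, a primary diagnosis of Major Depressive Disorder according to DSM-IV criteria". It asks for no atypical features and no threshold on the SIGH-SAD or its atypical items. The only DSM-IV specifier it uses is an exclusion: "the presence of the DSM-IV Seasonal Pattern specifier".

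The Primary Outcome measure section introduces the SIGH-SAD and says it is "equally applicable for assessment of nonseasonal depression with atypical features (as in the present study"). It adds: "The Hamilton and atypical symptom subscales of the SIGH-SAD can be analyzed separately or in combination".

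The Statistical analysis section assigns the SIGH-SAD, HAM-D6 and MADRS scores to repeated measures analysis of variance as secondary analyses. For the tertiary analyses, "response is defined as a decrease of ≥ 50% on the HADRS-17, HAM-D6, SIGH-SAD and MADRS scales", and the responder rates are also to be given as odds ratios and NNTs. The Atypical-8 is named in neither list.

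**The concern.** A percentage reduction is a workable response criterion when every patient starts well above zero. For overall or core depression severity, the diagnosis of major depression makes that likely. It gives no such protection to an eight-item subscale of atypical symptoms, because a patient can meet the diagnosis with few or none of them.

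At a baseline of 0 the outcome has no value. The patient must be left out, or counted as a non-responder who could never have responded. New atypical symptoms in such a patient cannot register in this outcome. At 1 or 2 the criterion is met by the smallest change the scale can record, so response there largely reflects rating noise, which is equal in both arms and hides a real difference.

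The analysis section supplies no alternative. A reader cannot tell whether the Atypical-8 is to be dichotomised, analysed as a score, or not analysed separately at all.

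**Working it through.** **The article's own figure.** The only design figure is the sample size, with α 0.05 two-sided, 0.80 (printed as β, read as power) and a standardised effect of 0.50, the lower end of the cited range. n per arm = 2 × (1.960 + 0.842)² / 0.50² = 62.8, which rounds up to 63 and matches the article. The present point does not depend on it.

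**The rule by baseline score.** No assumption is needed here. For an integer baseline b, the percentage reduction is (b − follow-up)/b, and the smallest qualifying fall is b/2 rounded up.

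| Baseline | Smallest fall that counts | As % of baseline |
|---|---|---|
| 0 | none (division by zero) | undefined |
| 1 | 1 | 100% |
| 2 | 1 | 50% |
| 3 | 2 | 67% |
| 4 | 2 | 50% |
| 6 | 3 | 50% |
| 8 | 4 | 50% |
| 10 | 5 | 50% |

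At a baseline of 2, a one-point fall is exactly 50%, so it meets both the wording under Secondary Outcome measures and the ≥ 50% in the analysis section.

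**Chance response at a given baseline.** Assume no true change and normal rating noise with an SD of change s, ignoring the floor at 0. The chance of response is Φ((0.5 − smallest fall)/s).

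- Baseline 1 or 2: Φ(−0.5/1) = 31% at s = 1; Φ(−0.5/2) = 40% at s = 2.
- Baseline 4: Φ(−1.5/1) = 7%; Φ(−1.5/2) = 23%.
- Baseline 8: Φ(−3.5/1) = 0.02%; Φ(−3.5/2) = 4%.

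**How many patients this could touch.** The article gives no Atypical-8 mean, SD, range or reliability, so everything in this step is assumed: a gamma-distributed true score plus normal error, rounded and limited to 0–26, test–retest correlation 0.8 and no true change, with 400,000 simulated patients per row. In each cell the first figure takes the SD as that of the true score, and the second takes it as that of the observed score.

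| Assumed mean (SD) | Baseline 0 | Baseline 1–2 | Noise response where computable |
|---|---|---|---|
| 2 (2) | 25% / 22% | 43% / 46% | 31% / 28% |
| 3 (2.5) | 16% / 13% | 33% / 35% | 25% / 22% |
| 4 (3) | 12% / 9% | 25% / 25% | 22% / 19% |
| 6 (3.5) | 5% / 3% | 13% / 12% | 14% / 11% |
| 8 (3.5) | 1% or less | 5% / 3% | 7% / 5% |
| 10 (4) | 1% or less | 2% / 1% | 5% / 3% |

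Of 126 patients, 25% is about 32 and 1% is about 1. The same rule on the HADRS-17, with an assumed mean of 18 and SD of 4.5, gives a noise response of 0.5% or less.

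**The two sections side by side.** Secondary Outcome measures lists response on the 29-item SIGH-SAD, Atypical-8, HAMD-6 and MADRS. Statistical analysis dichotomises the HADRS-17, HAM-D6, SIGH-SAD and MADRS. Apart from the primary scale, the difference is the Atypical-8. The first section lists the SIGH-SAD total and the Atypical-8 as separate outcomes, so naming the SIGH-SAD in the second does not clearly cover the subset.

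**The case against.** The strongest case on the other side accepts the arithmetic and disputes the consequences. Most of it stands.

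- A reader might infer that odds ratios and NNTs will be diluted. The article plans these only for the four scales in the analysis section, and the Atypical-8 is not one of them.
- A reader might infer that worsening on atypical symptoms is lost to the trial. It is lost to this one outcome. The eight items belong to the 29-item SIGH-SAD, whose scores go into a planned repeated measures analysis.
- A reader might infer that leaving out patients at 0 breaks the randomised comparison. That would follow only if they are dropped, and the article does not say so. Even then the selection would rest on a score taken before light therapy starts, which narrows the population but does not by itself bias the contrast between arms. How to handle zeros is also detail that an analysis plan may settle.
- A reader might take the parenthesis in the remark on the SIGH-SAD as a claim that all patients have atypical features, contradicting the entry criteria. It may refer only to nonseasonal depression, which the exclusion of the seasonal pattern does enforce. A descriptive remark is not made false because entry does not select for the feature, and deleting it would change no result.
- The practical size rests on unknown inputs. If most patients score 8 or more at baseline, the problem nearly disappears.

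What does not fall away is that the article positively fixes a percentage rule for a subscale whose baseline its entry criteria leave open, and that its two sections differ on whether the subscale is dichotomised. Neither is a matter of missing detail.

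**Conclusion.** The point holds as a minor one. That the rule is undefined at 0 and met by one point at 1 or 2 follows from the text and needs no assumption. So does the mismatch between the Secondary Outcome measures and Statistical analysis sections. How much it matters in practice runs from large to negligible, and the documents cannot settle where in that range this trial lies. The figures for the share at 0 and for noise response rest entirely on the assumed means, SDs, score range and test–retest correlation.

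Only one secondary outcome is affected. Nothing here calls into question the primary HADRS-17 analysis, the 63 patients per arm, or the responder analyses planned for the other scales.

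**What to change.** 1. Under Secondary Outcome measures, remove the Atypical-8 from the 50% response list, so that the list agrees with the scales dichotomised under Statistical analysis. Keep the 50% rule for the HADRS-17, HAM-D6, SIGH-SAD and MADRS.
2. Under Statistical analysis, add the Atypical-8 to the secondary analyses as a continuous score at T1 and T2, adjusted for T0. State that patients with a T0 score of 0 are included.

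Patients at 0 then contribute, and new atypical symptoms count. If a response rate on this subscale is still wanted, it needs a prespecified minimum baseline and a stated rule for patients below it, which would restrict the population it describes.

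The cost is a change of wording and the loss of one dichotomous secondary result. No new data are needed.

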### Adverse effects

At each visit and 4 additional times, subjects are systematically asked about possible side effects by the blind raters: early morning awakening, headache, agitation, drowsiness, irritability, tight muscles, nervousness, anxiety, tremor, dizziness, fatigue nausea, diarrhoea, dry mouth, anorexia, dyspepsia, constipation, excessive sweating, rash, asthenia, viral infection, upper respiratory infection, flulike syndrome, nasal congestion and hot flushes [47]. Each item is rated as absent, mild, moderate or severe. The subjects were instructed to report any side effects that could have jeopardized the blindness of the raters (such as eye strain, a side effect characteristic of bright light) to a nonblind research assistant who simply tabulated these side effects.

### Endocrine measures

1. Activity of the HPA-axis was assessed by free cortisol assessment using 8 saliva samples per respondent per time. As a measure of a natural "stress" response of the HPA-axis, the morning cortisol awakening response (CAR) is assessed by taking saliva samples at T0, T1 and T2 (at get-up time plus 30 minutes, plus 60 minutes, plus 90 minutes, plus 120 minutes), and the cortisol evening curve (bedtime minus 4 hours, minus 3 hours, minus 2 hours, minus 1 hour). Saliva samples are collected using cotton swaps (Salivettes, Sarstedt, Germany). Subjects are instructed to be seated during the last 15 minutes before saliva collection. During the entire sampling period, subjects can watch TV or perform leisure activities. Eating and drinking (with the exception of coffee, tea, chocolate, and bananas), and smoking will be permitted. Saliva containers are kept in the patient's refrigerators and are to be collected by the psychometrist the next day after psychometry, which are delivered to the clinical labwhere it is spinned down and stored at -85°C. Cortisol will be assayed on an Elecsys using a standard cortisol kit (Roche). Saliva samples are frozen in order to do all measurements at once.

2. To determine a patients circadian phase position the Dim Light Melatonin Onset (DLMO; the time point when melatonin secretion rises over a predefined threshold in the evening, under experimental dim light conditions) will be calculated after measuring the melatonin evening curve using measurements in saliva samples (bedtime minus 4 hours, minus 3 hours, minus 2 hours, minus 1 hour) at T0, T1 and T2.

3. Total cortisol excretion at T0, T1 and T2 will be determined using 24-hour urine collections. Collections are carried in the participants' own homes, following procedures provided through detailed written and verbal instructions. Urine is collected for 24 hours after the first voided urine following awakening, and included the first voided urine on the following day. Three liter polyethylene collection bottles were used. The completeness of data collection is ascertained by measurements of the 24-hr urine volume and creatinine excretion. Only participants demonstrating good compliance, using this quality control step, will be included in the analyses. The urinary free cortisol (UFC) will be determined by radioimmunoassay using a commercially available (Coat A Coat, Diagnostic Product Corporation (DPC), Los Angeles USA) antibody specific for cortisol and I-125-labeled antigen. Urinary measurements are performed by the laboratory at arrival.

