## Methods and design

### General objectives

The purpose of this study is to investigate the following hypotheses:

1. Treatment with bright light improves mood, sleep, concentration and self-sufficiency of elderly depressed subjects. This clinical improvement is accompanied by decreases in cortisol and increase in melatonin concentrations.

2. The eventual beneficial effect of bright light treatment can be predicted by the presence of sleep-wake rhythm disturbances as found using muscle activity registration, and by cortisol and melatonin concentrations in saliva and urine over the day and the night.

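### The cortisol awakening response is to be measured without a saliva sample at awakening, so the rise from awakening cannot be computed

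*Protocol article*

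**What the plan says.** All sampling details are in the Endocrine measures section of the protocol article.

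- Count: HPA-axis activity is measured by "free cortisol assessment using 8 saliva samples per respondent per time".
- Morning: "the morning cortisol awakening response (CAR) is assessed by taking saliva samples at T0, T1 and T2", at these times: "at get-up time plus 30 minutes, plus 60 minutes, plus 90 minutes, plus 120 minutes".
- Evening: "the cortisol evening curve (bedtime minus 4 hours, minus 3 hours, minus 2 hours, minus 1 hour").
- Melatonin: the dim light melatonin onset (DLMO) is defined as "the time point when melatonin secretion rises over a predefined threshold in the evening, under experimental dim light conditions". It is to be calculated from saliva at the same four evening times, at each of the three assessments.
- Setting: saliva is kept in patients' own refrigerators. The cortisol item adds: "During the entire sampling period, subjects can watch TV or perform leisure activities".
- Urine: 24-hour collections are assayed for cortisol, with volume and creatinine used to check completeness.

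Under General objectives, hypothesis 2 says that benefit can be predicted by rhythm disturbances on activity registration and "by cortisol and melatonin concentrations in saliva and urine over the day and the night".

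**The concern.** A response to awakening is a change that starts from the value at awakening. If the first sample comes 30 minutes after the patient has got up, the starting value is unknown. A high value at that point could mean a large rise, or a high level already present on waking. The two cannot be told apart, and a treatment difference in one could be reported as a difference in the other.

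The anchor adds a second uncertainty. Getting up is not waking, and the article's Actigraphy section keeps Sleep End and Get Up Time apart. Sleep is one of the things treatment is meant to improve (hypothesis 1). If treatment changes how long patients lie awake before rising, the samples shift relative to waking, and a change in timing could look like a change in cortisol.

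At stake is the meaning of one named HPA-axis measure. The clinical efficacy comparison is not at stake.

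**Working it through.** **1. Reproduce the stated count.** Inputs, from Endocrine measures: morning times +30, +60, +90 and +120 minutes from get-up; evening times −4, −3, −2 and −1 hours from bedtime.

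- As listed: 4 + 4 = 8, which equals the stated 8.
- If getting up were itself a sampling point: 5 + 4 = 9, which contradicts the stated 8.

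The article's own total therefore settles the reading: the earliest morning sample is at +30 minutes.

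**2. What can be computed.** Write C(t) for cortisol at t minutes after awakening. The rise from awakening is C(t) − C(0). With C(0) never observed, it is not available for any patient at any assessment: 0 of 126 at T0, at T1 and at T2. Three quantities remain: the level at each of four times, the area over 120 − 30 = 90 minutes, and the decline over that interval.

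**3. The anchor.** If a patient wakes w minutes before getting up, the first sample falls 30 + w minutes after waking. The article gives no figure for w. Purely as an assumed range, w from 0 to 60 minutes puts the first sample 30 to 90 minutes after waking. So even the post-awakening curve is aligned to waking only up to an unknown shift.

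**4. Tubes after a change.** Moving one morning sample keeps 4 + 4 = 8 per assessment and 3 × 8 = 24 per patient. Adding one instead gives 9 per assessment and 3 × 9 = 27 per patient. Over 126 patients that is 126 × 24 = 3,024 against 126 × 27 = 3,402 tubes.

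**5. Melatonin window.** The evening samples run from −4 h to −1 h, a span of 3 hours at hourly spacing. A threshold crossing inside the span can be located to within an hour. One before −4 h or after −1 h is known only to lie on that side. The article gives no figure for how many onsets fall outside, so this has no size here.

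**6. Hypothesis 2 against the measures.** The hypothesis names two hormones, two fluids, and day and night. The measures described give cortisol in morning saliva, evening saliva and 24-hour urine, but melatonin in evening saliva only. No urinary, daytime or night-time melatonin is described.

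**The case against.** The article never says that the endpoint is a rise from a waking value. It calls the measure a natural stress response of the HPA-axis, and level, area and decline from +30 to +120 minutes are legitimate summaries. Hypothesis 1 speaks of hormone concentrations, which the saliva samples and 24-hour urinary cortisol supply; hypothesis 2 also draws on activity registration. Actigraphic Sleep End gives an estimate of waking, which partly answers the anchor problem. The schedule is the same in both arms, and these measures are neither the primary nor the listed secondary outcomes.

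Most of this stands and limits the weight of the point. It does not rescue the label: a response to awakening cannot be read from samples that all come later, and an estimated waking time does not supply a cortisol value at that time. Nor is this a detail left to a fuller document, since the article fixes both the times and the count.

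A reader might go further and infer that DLMO cannot be obtained either, because patients sample at home with television allowed. The article does not support that. It names dim light in its definition, and a crossing inside the evening window can be located. The television sentence stands under the cortisol item and says nothing about room lighting. A lighting instruction may well be in the full protocol or the patient's instruction sheet. A reader might also infer that both hypotheses collapse; they do not, because neither rests on these two measures alone.

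On hypothesis 2, the phrase can be read collectively, with urine meant for cortisol only. That makes it a wording matter, but one worth settling.

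**Conclusion.** The point holds for the cortisol awakening response. As written, the schedule gives the rise from awakening in none of the 126 planned patients at any of the three assessments, and the remaining samples are timed from get-up, not from waking. This rests on two things: that a response to awakening means a change from the value at awakening, and that the stated 8 samples are the listed 4 + 4, which the count confirms.

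The melatonin issues are minor: light exposure during evening sampling should be checked, onsets outside the window are censored, and hypothesis 2 is worded more broadly than the measures described.

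The consequence is confined to the mechanistic and predictive questions. The HADRS-17 analysis and the target of 63 patients per arm do not depend on it. It is worth correcting because the correction is cheap and the measure would otherwise carry a name it does not earn.

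**What to change.** Move one morning sample, for example the one at 120 minutes, to the moment of awakening, and time the other three from awakening. The count stays at 8. Patients should write down their waking time, and actigraphic Sleep End can serve as a check. The instruction to sit for 15 minutes before each collection cannot apply to the waking sample and needs an exception.

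The cost is a revised instruction sheet, loss of the 120-minute value, and no awakening value for patients already sampled, so the rise could be analysed only in those sampled after the change. Adding a tube instead would keep the 120-minute value at 3 extra samples per patient.

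If sampling cannot change, report the measure as post-awakening cortisol, state that it is timed from get-up, and do not interpret it as an awakening response.

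Smaller changes:

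- Use the lux-meter in the wrist actimeter, already worn throughout (Compliance section), to check light during evening melatonin sampling.
- Treat melatonin onsets before bedtime minus 4 hours or after bedtime minus 1 hour as censored. Do not move the last evening sample to bedtime: that would leave a two-hour gap from −2 h to 0.
- Reword hypothesis 2 so that it names evening saliva melatonin, saliva cortisol and 24-hour urinary cortisol; if urinary or night-time melatonin is intended, describe how it is measured.

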### Compliance

Compliance to light therapy is retrospectively measured by lux-meters that were built in the wrist-worn actimeters patients wear during the entire protocol. Subjects are instructed by a protocol-blinded instructor to sit at their table, with the light boxes put at a distance of approximately 40 cm from the eyes. During therapy, subjects sit at the table to have breakfast or do some reading (e.g. news paper). Participants will be asked to note their compliance in their trial-diaries.

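### Eating, most drinks and smoking are expressly permitted during saliva sampling with no stated abstention before a swab, so salivary cortisol can be noisier and, as a baseline predictor, confounded

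*Protocol article*

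**What the plan says.** Endocrine measures, item 1, describes HPA-axis activity by "free cortisol assessment using 8 saliva samples per respondent per time". The morning samples are taken "at get-up time plus 30 minutes, plus 60 minutes, plus 90 minutes, plus 120 minutes"; the evening samples are taken 4, 3, 2 and 1 hours before bedtime. This is done at T0, T1 and T2.

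The instructions on conduct are three consecutive sentences. The first fixes posture: "Subjects are instructed to be seated during the last 15 minutes before saliva collection". The second concerns activity: "During the entire sampling period, subjects can watch TV or perform leisure activities". The third concerns intake: "Eating and drinking (with the exception of coffee, tea, chocolate, and bananas), and smoking will be permitted". No other instruction on food, drink, smoking or mouth rinsing is given.

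Elsewhere the protocol takes care over endocrine interference. Inclusion and exclusion criteria bar diseases that could affect the HPA axis and "any drugs (e.g. corticosteroids, cyclosporin A) known to interfere with endocrine function". Endocrine measures, item 3, checks the completeness of the 24-hour urine collections by volume and creatinine and analyses only compliant participants.

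Under General objectives, cortisol has two roles. Hypothesis 1 expects it to fall as patients improve. Hypothesis 2 uses it, in saliva and urine, to predict who benefits.

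**The concern.** This is a stated permission, not a detail lost when the protocol was condensed into an article. The authors defined an interval before each swab and filled it with posture alone, then allowed eating, smoking and all but a few drinks.

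The premise is general physiology and assay practice, which the documents do not discuss: a recent meal or cigarette can change cortisol acutely, and residue in the mouth can affect a saliva assay. On that premise, two patients with the same HPA regulation can return different curves because one ate or smoked shortly before a swab.

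The morning series is the most exposed, because the two hours after getting up usually include breakfast. That series is the protocol's measure of the cortisol awakening response. At stake are the precision of the cortisol comparison under hypothesis 1 and the meaning of baseline salivary cortisol under hypothesis 2.

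**Working it through.** The plan gives no figure for the effect of intake or smoking on cortisol, so there is none to reproduce. The check compares the instructions, counts the exposed samples, and shows what added noise would do under stated assumptions.

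**1. Samples under the rule.** 4 morning + 4 evening = 8 per time point, which agrees with the stated number. 8 × 3 = 24 per patient, of which 4 × 3 = 12 are morning samples.

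**2. What is controlled before a swab.**
- Posture: seated for 15 minutes.
- Food: chocolate and bananas excepted, otherwise permitted; no interval stated.
- Drink: coffee and tea excepted, otherwise permitted; no interval stated.
- Smoking: permitted; no interval stated.
- Mouth rinse or record of intake times: not mentioned.

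**3. How much of the morning lies just before a swab.** The four 15-minute windows run from 15 to 30, 45 to 60, 75 to 90 and 105 to 120 minutes after getting up. Together they cover 4 × 15 = 60 of 120 minutes, or half. One short breakfast would usually overlap one window rather than all four, so not every morning sample is affected by residue or very recent intake. Any slower effect of a meal on later samples would not be confined to these windows.

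**4. Effect of added noise on a comparison of arms (illustration).** Assume that uncontrolled intake and smoking contribute a share v of total cortisol variance, equally in both arms. A noise-free standardised difference of 0.50 is then seen as 0.50 × √(1 − v). The 0.50 is borrowed from the Sample size section, where it refers to depression ratings; at two-sided α 0.05 and power 0.80 it reproduces the planned 63 per arm. Neither 0.50 nor v is known for cortisol.
- v = 0: difference 0.500, power with 63 per arm 80%, n per arm for 80% power 63.
- v = 0.05: 0.487, 78%, 67.
- v = 0.10: 0.474, 76%, 70.
- v = 0.20: 0.447, 71%, 79.
- v = 0.30: 0.418, 65%, 90.

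**5. Effect on a baseline predictor.** If the same share v is pure random error, the slope of benefit on baseline cortisol shrinks by the factor 1 − v, that is to between 0.95 and 0.70 of its value for v from 0.05 to 0.30. Smoking and breakfast habits are not pure random error, however. They are stable traits that may themselves relate to severity or outcome, and randomisation does not balance them across levels of baseline cortisol. The association can then be confounded as well as weakened, and the direction cannot be stated.

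**6. Bias between arms under hypothesis 1.** The instruction is identical in both arms. A shift common to both arms cancels in the comparison. Bias would require the allocated light to change eating or smoking on sampling days differently by arm, and the documents give nothing from which to estimate that.

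**The case against.** The strongest reply is that the permission describes the sampling day as a whole, since it follows a sentence about the entire sampling period, and that a short interval before each swab or a mouth rinse is patient-instruction detail that an article may omit. This stands in part. A reader might infer that patients may eat or smoke right up to the swab; the article does not say so, and the full protocol may hold an interval. What it does show is an express permission beside a 15-minute rule that covers posture only.

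A reader might also infer a bias against hypothesis 1: patients who improve eat breakfast again, and their cortisol rises for that reason. The documents do not support this. Improvement could equally reduce smoking, which on the same premise would push the other way. The Primary Outcome measure section refers to atypical features in this population, so one direction of appetite change cannot be assumed. Any such effect would also have to differ by arm.

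The Compliance section is weak evidence on sampling days. Its remark that "During therapy, subjects sit at the table to have breakfast or do some reading" describes light sessions, whereas T0 precedes treatment, T1 follows its completion and T2 comes three weeks later. It shows only that breakfast early in the morning is expected in this population.

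Finally, cortisol is neither the primary nor a listed secondary outcome, and 24-hour urinary cortisol at the same three time points does not depend on mouth residue or on when a meal falls relative to a swab. In unsupervised home sampling of elderly depressed patients, strictness also has a price. All this stands and limits the weight of the point, but does not remove it: salivary cortisol is named in hypothesis 2, and the awakening response is measured only in saliva.

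**Conclusion.** The point holds as a weakness of the salivary cortisol measurement. Eating, most drinks and smoking are permitted during sampling with no stated abstention before a swab, so the values can be noisier, especially in the morning series. Baseline salivary cortisol as a predictor of benefit can also be confounded by differences in eating and smoking between patients.

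The conclusion rests on two assumptions: that recent intake and smoking can affect salivary cortisol, and that the full protocol adds no stricter instruction. The documents support neither a size nor a direction of bias between arms; the power and slope figures above only illustrate assumed noise shares of 5% to 30%. HADRS-17 and the sample size are unaffected, and urinary cortisol does not share the problem of mouth residue or swab timing. The change is worth making because it is cheap and because intake that was not recorded on the day cannot be reconstructed when the frozen samples are assayed together.

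**What to change.** In Endocrine measures, item 1, replace the sentence permitting eating, drinking and smoking with an extension of the seated rule. In the 15 minutes before each swab there should be no food, no drink except water, no smoking and no tooth brushing, with a water rinse at the start of that interval. The existing exceptions (coffee, tea, chocolate, bananas) can stay. The 30-minute morning spacing leaves 15 minutes after each of the first three swabs, and breakfast can be taken then.

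Add to the sampling form the times of meals and cigarettes on each sampling day, completed in the same way at T0, T1 and T2. Use these times to flag affected samples and to exclude or adjust for them in a sensitivity analysis of salivary cortisol.

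Both parts are needed. The abstention deals mainly with residue and very recent intake. A meal eaten directly after one swab may still influence the next, and only the recorded times allow earlier meals and smoking to be taken into account. If the full protocol already sets such an interval, the article should state it.

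Cost: one changed instruction, a few extra entries on a form, and a small added burden for patients on three sampling occasions.
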